**Methods/design:**

A randomized controlled trial will be undertaken within the stroke rehabilitation wards of the Second Affiliated hospital of Anhui University of Traditional Chinese Medicine, Hefei, China. The study participants will be stroke survivors who meet inclusion criteria for the study, primarily: able to participate, no more than 4 months after stroke and walking independently before stroke. Participants will all receive standard local rehabilitation and will be randomly assigned either to receive regular feedback about activity levels, relative to a daily goal tailored by the smart watch over five time periods throughout a working day, or to no feedback, but still wearing the Smart watch. The intervention will last up to 3 weeks, ending sooner if discharged. The data to be collected in all participants include measures of daily activity (Smart watch measure); mobility (Rivermead Mobility Index and 10-metre walking time); independence in personal care (Barthel Activities of Daily Living (ADL) Index); overall activities (the World Health Organization (WHO) Disability Assessment Scale, 12-item version); and quality of life (the Euro-Qol 5L5D). Data will be collected by assessors blinded to allocation of the intervention at baseline, 3 weeks or at discharge (whichever is the sooner); and a reduced data set will be collected at 12 weeks by telephone interview. The primary outcome will be change in daily accelerometer activity scores. Secondary outcomes are compliance and adherence to wearing the watch, and changes in mobility, independence in personal care activities, and health-related quality of life.

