Patients with stroke tend to be discharged from in-patient rehabilitation at the Second Affiliated Hospital of Anhui University of Traditional Chinese Medicine after 2–3 weeks. Therefore, the length of the inpatient intervention phase will vary between participants but will be no more than 3 weeks. Activity score (i.e. counts) are summarised at five time points (i.e. at 2-hour increments) throughout the day. Summary analysis, from each time point and from the whole day will be used in the analysis.

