For outcome data, the linear mixed models (LMM) procedure in SAS 9.4 will be used to determine the mean changes in measures, as response variables, according to two intervention regimes (intervention and control) and three repeated measurements, using baseline as a covariate. Distribution of the data will be checked according to various methods of analysis, which are employed at different stages of the study. The analysis of outcome, which will be based on LMM, assumes a Gaussian distribution that can be checked and tested by standard methods. However, we also note that LMM is, in general, quite robust to violation of the distributional assumptions.

This model treats all factors as categorical, and so different types of data can be used. Further and based on the differences in least squares (marginal) means between the two groups (intervention vs control), provided by LMM analysis, power, effect size (Cohen’s d) and their 95% non-central confidence limits will be calculated. Analysis will be used for each outcome measure. The “group” term is the intervention group; the “time” term is the assessment time point. The group-by-time interaction effect will reveal if there is a greater change over time in one group compared with the other.

For a sample size estimate, we used a conservative estimate of the standardised effect size of change in physical activity levels from the initial assessment to discharge from inpatient rehabilitation (i.e. the first phase of the study) as our primary outcome of interest. Our pilot work suggests an effect size of 0.12, and for alpha 0.05 and power 0.95 for repeated measures with three measurement points, we expect a sample of 182 to be adequately powered. From pilot work we expect 10% to drop out, and so we propose to recruit 200 patients.

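### Three repeated measurements with baseline as covariate do not fit the schedule: either a time-averaged effect size is diluted or the group-by-time term misses a constant effect, and the watch outcome has no defined third point

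*Protocol article*

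**What the plan says.** **Model (Data handling and analysis).** A linear mixed model in SAS fits each outcome "according to two intervention regimes (intervention and control) and three repeated measurements, using baseline as a covariate". What is modelled is change: the procedure "will be used to determine the mean changes in measures, as response variables". In it, "the “time” term is the assessment time point". Power, Cohen's d and its non-central confidence limits are then "based on the differences in least squares (marginal) means between the two groups", with no time named. The text adds: "The group-by-time interaction effect will reveal if there is a greater change over time in one group compared with the other". This analysis is to serve every outcome.

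**Schedule.** The abstract has data collected "at baseline, 3 weeks or at discharge (whichever is the sooner"), plus a shortened set at 12 weeks by telephone. The Data collected section gives the same three occasions.

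**Primary outcome.** This is the change in daily watch activity score. The watch is worn on weekdays in hospital for up to 15 days (Design). Day 1, without feedback in either group, is the baseline (Intervention section). Use at home was not possible (Discussion). On the use of these data, the Data collected section says: "Summary analysis, from each time point and from the whole day will be used in the analysis". The time points in that sentence are the five periods of a day, not assessments.

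**Sample size.** The target is the change in activity from the initial assessment to discharge: effect size 0.12, alpha 0.05, power 0.95, three measurement points, N = 182, raised to 200 for 10% dropout.

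**The concern.** The time factor is the assessment, and the article names only three assessments, one of which is baseline. Three repeated measurements on that schedule must include baseline, yet baseline is also the covariate. The response is moreover described as change, which is zero at baseline by construction and leaves two informative occasions.

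The article offers two quantities as the treatment effect: a group difference in marginal means and the group-by-time term. Which of them is sound depends on whether baseline is a response. At stake are the size of the reported effect with its interval, and the meaning of the test that is said to show greater change in one group. For the primary outcome there is a further mismatch: the third assessment, at 12 weeks, yields no watch score.

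**Working it through.** **1. The plan's own figure.** Inputs: f = 0.12, alpha 0.05, power 0.95, m = 3 points and k = 2 groups. Not stated, so assumed: correlation rho = 0.5, sphericity, 1:1 allocation.

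- Group-by-time test: lambda = f²·N·m/(1 − rho) = 0.0144 × 182 × 3/0.5 = 15.72, with df 2 and 360. Power is 0.952, and 182 is the smallest even N that reaches 0.95. The stated figure is reproduced; the within-subject time test with two groups gives the same N.
- Time-averaged group effect: lambda = f²·N·m/(1 + (m − 1)·rho). At the same f this needs N = 604, and power at 182 is 0.505.

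The sizing therefore matches the interaction type of test, not a time-averaged marginal difference.

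**2. Baseline as both response and covariate.** Let d1 and d2 be the true effects at 3 and 12 weeks. Randomisation makes the expected group difference at baseline zero. The difference averaged over three times is (0 + d1 + d2)/3, against (d1 + d2)/2 for the follow-ups, a ratio of 2/3.

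- Constant 0.40 SD: (0 + 0.40 + 0.40)/3 = 0.27 SD.
- 0.40 SD at 3 weeks only: (0 + 0.40 + 0)/3 = 0.13 SD.

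A simulation (100 per arm, compound symmetry, rho 0.5, 500 runs, true effect 1 at both follow-ups) agrees:

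| Quantity | Baseline is a response | Baseline is covariate only |
|---|---|---|
| Time-averaged difference (SD over runs) | 0.668 (0.066) | 0.998 (0.099) |
| Estimate / SD | 10.1 | 10.1 |
| Difference at 3 weeks | 1.004 | 0.996 |
| 3 weeks minus baseline contrast | 1.004 | not available |

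Relative to the 3-week effect, the averaged estimate loses 33% if the effect is maintained at 12 weeks, 50% if it halves, 67% if it is lost, and 17% if it grows to 1.5 times. Results at rho 0.3 and 0.7 were alike.

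**3. Baseline as covariate only.** The responses are then 3 and 12 weeks, and the group-by-time contrast is d1 − d2. For a constant effect this is 0.40 − 0.40 = 0, which is the null hypothesis, so the rejection rate equals alpha. Simulation (N = 180, rho 0.5, 4,000 runs) gave 0.051. The marginal mean difference is unbiased here.

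**4. The watch outcome.** The assessment schedule gives this outcome two points, baseline and discharge. The formula in step 1 with m = 2 and f held at 0.12 gives:

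| rho (assumed) | N, three points | N, two points | Power, two points, N = 182 | Power, two points, N = 160 |
|---|---|---|---|---|
| 0.3 | 252 | 318 | 0.777 | 0.722 |
| 0.5 | 182 | 228 | 0.896 | 0.855 |
| 0.7 | 110 | 138 | 0.986 | 0.974 |

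The 160 is the final recruitment in the Trial status section. With 10% dropout from it (144), two-point power at rho 0.5 is 0.816.

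**The case against.** The strongest reply is that this is an ambiguity in a condensed article and not a proven error. The three measurements are never listed, the schedule figure is not shown, and a response defined as change would not normally have a baseline row. Three in-hospital watch summaries are also conceivable. The exact LS-mean contrast is often left to an analysis plan. All of that is fair, and it is why the double use of baseline is called apparent here.

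Three stronger readings are tempting, but the documents do not support them.

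- **Both faults occur together.** They exclude each other. With baseline as a response, the interaction contrast is undiluted; with baseline as covariate only, the marginal mean is correct. One of the two named quantities is sound on either reading.
- **The estimate always shrinks by a third or more.** Dilution needs LS means averaged over all three times, which the article does not state. Means per time point show none, and the test ratio is unchanged. Against the 3-week effect the loss is below a third if the effect grows.
- **The model cannot be fitted to the primary outcome.** Daily scores with a Day 1 baseline exist, and a mixed model fits them. The gap is that the three points are not named.

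What stands is that no reading makes the stated model, the assessment schedule and both stated quantities agree.

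**Conclusion.** The point holds as an inconsistency in the stated analysis, not merely as absent detail. If baseline is a response, a time-averaged group difference, and a Cohen's d formed by dividing it by an outcome SD, is two-thirds of the follow-up average. The article does not state the standardiser; a d rebuilt from the test statistic would not be diluted. If baseline is only a covariate, the group-by-time term has about 5% power against a constant effect and does not show what the article says it shows.

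For the primary outcome, neither the three-assessment model nor the three-point sizing matches a score that stops at discharge, unless in-hospital points are defined. If there are only two points, the required N at rho 0.5 is 228 rather than 182.

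The two-thirds ratio is algebra and needs only time-averaging over three occasions. The 0.27 and 0.13 SD figures illustrate an assumed 0.40 SD effect. The sample sizes rest on the assumed correlation, sphericity, equal allocation and f held at 0.12. Any precision gained by averaging many watch days, and any choice of random slopes, are optional refinements that rest on assumptions and are not part of the error.

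**What to change.** 1. Use only post-baseline values as responses, with baseline as covariate (the Day 1 score for the watch outcome).
2. Report the adjusted group difference at each time. Name the 3-week/discharge difference as the main contrast and the source of Cohen's d and its limits. Use neither the group-by-time term nor a mean that includes baseline for this purpose.
3. Describe the group-by-time term as what it then is: a test of whether the effect differs between follow-up times.
4. For the watch score, state which in-hospital days or weeks enter the model, and keep the stated change from initial assessment to discharge as the target.
5. State which contrast and which measurement points the sample size of 182 refers to, and the correlation assumed.

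The cost is a revised paragraph and a short change to the SAS code. No new data are needed. Recruitment has closed, so item 5 clarifies what power can be claimed and does not change the sample.

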A third limiting factor arises from the funding and timing of inpatient rehabilitation in Hefei, which starts quite late after stroke and is limited to 2 or 3 weeks of inpatient rehabilitation, limiting the time the intervention can be applied. By the time a person is admitted, they have already established a pattern of behaviour. Also, it may take at least 1 week to become familiar with the device and its purpose and, because changing behaviour takes time, the intervention may be too short to lead to any detectable difference between the groups. It was not possible to provide the watch for use at home, mainly for practical reasons (daily data downloads and recharging). Ideally the intervention should be continued over many weeks.

The research funding was limited. The research data were collected by the ward doctors, who were specifically trained and collected the clinical data as part of their normal work. However, this limited the options of using more fixed procedures, for example when checking cognitive ability. This will not cause any bias, but may slightly limit generalizability.

Last, it has been assumed that increasing general, non-specific activity levels will lead to specific changes in mobility and independence is activities. This assumption is reasonable, but the strength of the relationship is unknown and a much larger study may be needed to show any actual benefit.

One strength is that, according to our calculations, the study is adequately powered; we will recruit about 200 patients. Second, the study is embedded with daily clinical routines in a busy hospital, such that if the intervention is effective, it should be easy to continue the intervention.

If this study does not show an effect, there will still be worthwhile knowledge generated. The study will give an estimate of variance in the measures used, which will help in future power calculations. It will discover whether a short episode of feedback on activity set against goals might have an effect. Failure to find an effect should not be taken as proving the intervention is ineffective, given the limitations identified. The study will give information about the feasibility of collecting data in a trial set within a standard rehabilitation programme in China (Additional file 1).

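### Power is to be calculated from the observed group differences, so it only restates each p-value; drop it or compute it at the planning effect

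*Protocol article*

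**What the plan says.** After describing the linear mixed model, the Data handling and analysis section lists what is to be derived from the fitted between-group differences ("provided by LMM analysis, power, effect size"). The effect size is Cohen's d. Interval estimates are planned for both quantities: "and their 95% non-central confidence limits will be calculated". A further sentence extends this to all outcomes: "Analysis will be used for each outcome measure". The input to this power figure is therefore the difference estimated from the trial data. No purpose is given for it.

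The same section has a separate a priori calculation. It starts from the pilot ("Our pilot work suggests an effect size of 0.12"), sets alpha at 0.05 and power at 0.95 with three repeated measurements, and arrives at 182 participants. The recruitment target was 200. Trial status reports that recruitment ended at 160.

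On a null result the Discussion says: "Failure to find an effect should not be taken as proving the intervention is ineffective, given the limitations identified". It also counts the trial's power among its strengths.

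**The concern.** Power is a property of the design at an effect fixed in advance. If the estimated effect is put in its place, the result depends on the data only through the test statistic, and so carries the same information as the p-value on another scale. It cannot show which effects the data rule out.

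The figure is also low for every non-significant result by construction, even where the design was sensitive to its planning effect. Recruitment stopped at 160 of 200, so a reader who meets a low power figure beside a null may put the null down to sample size. What is at stake is how the results are read, not the results themselves.

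**Working it through.** **Inputs from the article.** Effect size 0.12, alpha 0.05, power 0.95, three measurement points, sample 182, 10% dropout (Data handling and analysis); two groups (Design); 160 recruited (Trial status).

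**Assumptions not in the article.** 0.12 is Cohen's f; correlation between repeated measures ρ = 0.5; sphericity; equal arms; two-sided alpha.

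**1. The plan's own figure.** For the group-by-time interaction with m = 3 times, the non-centrality is λ = f² × N × m / (1 − ρ), with 2 and 2(N − 2) degrees of freedom.

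- N = 182: λ = 0.0144 × 182 × 3 / 0.5 = 15.72, power 95.2%. The smallest even N reaching 95% is 182, so the stated figure is reproduced.
- N = 160: λ = 13.82, power 92.2%.
- N = 144 (160 less 10%): λ = 12.44, power about 89%.

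These depend on ρ. At N = 160, power is 65% for ρ = 0, 81% for ρ = 0.3 and 99% for ρ = 0.7. Of the values tried (0, 0.3, 0.5, 0.7, 0.8), only 0.5 returns 182. Reading 0.12 as Cohen's d for a simple comparison of two means does not fit: it gives about 12% power at 182.

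**2. Observed power as a function of p.** For a two-group (1-df) contrast, let z be the normal deviate of the two-sided p-value. Observed power is P(Z > 1.96 − z) + P(Z < −1.96 − z). For p = 0.20, z = 1.282, and the sum is 0.2488 + 0.0006 = 0.249.

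| Two-sided p | 1-df contrast | 2-df interaction, N = 160 |
|---|---|---|
| 0.01 | 0.73 | 0.78 |
| 0.05 | 0.50 | 0.58 |
| 0.10 | 0.38 | 0.47 |
| 0.20 | 0.25 | 0.34 |
| 0.50 | 0.10 | 0.17 |

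Repeating the 1-df column with the non-central t at N = 40, 142, 160, 182 and 1000 changes no value at p ≥ 0.05 by more than 0.005. Sample size has almost no influence once p is known.

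**3. What the confidence limits add.** Take 80 per arm and p = 0.20. Then d = 0.20 (95% limits −0.11 to 0.51). Power is 25% at the estimate, and 10% and 90% at the two limits for d. At p = 0.50, d = 0.11 (−0.20 to 0.42); power is 10% at the estimate but 25% and 75% at the limits. If the limits are carried over in this way, the estimate falls outside them, because two-sided power does not increase steadily across an interval that contains zero. The interval for d is interpretable; the one for power is not.

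**4. The contrast.** Under the assumptions of step 1, a design with about 90% power for its planning effect would report 25% for a two-group contrast with p = 0.20.

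**The case against.** The strongest reply is that this is one redundant descriptive figure beside an adequate one. Cohen's d with 95% limits is already planned for each outcome, so a reader can see from it which effects are excluded. No estimate, test, error rate or sample size changes. All of this stands and limits the severity.

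A reader might also infer that the sponsor means to use low power to explain away a null. The article does not say so. The Discussion's caution, "Failure to find an effect should not be taken as proving the intervention is ineffective, given the limitations identified", rests on its listed limitations, which are mostly about wear time, the goal algorithm and the short intervention period. Its remark that a larger trial may be needed concerns whether more activity carries over into mobility and independence, not the primary activity outcome. Misreading is a foreseeable consequence, not a documented intention.

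Nor does a 50% ceiling apply to every non-significant result. It holds for 1-df contrasts. The text bases power on two-group differences, so those figures probably apply, but the section also names a group-by-time interaction, for which the ceiling is about 58%.

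What the reply leaves standing is that the power figure is a stated analysis for every outcome, has no stated purpose, and adds nothing to the p-value.

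**Conclusion.** The point holds as a reporting fault of low to moderate severity. That observed power is one-to-one with p needs no assumption about this trial: about 50% or less for any non-significant two-group contrast, and about 58% or less for the 2-df interaction. The comparison with real sensitivity (about 92% at 160, about 89% at 144) does rest on 0.12 being Cohen's f with correlation 0.5, which the article does not state but which reproduces its 182.

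The documents do not support the stronger readings that the analysis is invalid or that the sponsor plans to discount a null on grounds of observed power.

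**What to change.** Delete power from the calculations made after the model is fitted. Keep the planned adjusted difference and Cohen's d with 95% limits, and add one sentence per outcome on whether the interval excludes the effect the trial was sized for. If power is reported at all, compute it for the pre-specified effect at the achieved sample size.

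The sponsor should define that effect in outcome units for its three-time-point design. Converting 0.12 as 4 × 0.12 = 0.48 SD is tempting but belongs to two time points. With three points, f = 0.12 and ρ = 0.5 (so the SD of change equals the SD), write the two groups' deviations as ±a at each time, with f² the mean of a²:

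- Step pattern, a = (−2c, c, c): c = 0.12/√2 = 0.085, and the between-group difference in change is 6c = 0.51 SD.
- Linear pattern, a = (−c, 0, c): c = 0.12 × √1.5 = 0.147, and the difference is 4c = 0.59 SD.

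The threshold thus depends on a pattern that the article does not give, and 0.48 SD should not be used.

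Cost: one word removed and one sentence added, with no change to data, design or model.

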## Discussion

This study investigates whether setting personalized activity goals derived from and coupled with personal and early feedback on the amount of activity undertaken throughout each day can enhance self-generated activity levels, and whether any increase is associated with improved functional outcomes. The study design integrates the novel intervention into current practice which ensures that the results should be generally applicable. This discussion will cover acknowledged weaknesses and limitations, some arising from technological and financial limitations and others, which follow on from new information published after the protocol was finalized in July 2015. The discussion will also cover strengths and potential outputs in terms of new knowledge.

Technological and financial limitations underlie many of the weaknesses. The watch is only worn during the five working days and only for nine working hours each day. Ideally the watch would record activity and provide feedback throughout the whole time a patient is awake, including weekends and evenings. This limitation reflects constraints associated both with the watch and with the setting. Data storage is limited, which means that only 20% of the activity can be recorded. In addition, download of data is required each day, which requires a trained person, who is only available in working hours. Third, the watch needs charging each day, again requiring a trained person. With advances in technology these constraints should be overcome.

The goal-setting algorithm designed to make allowance for natural daily routines such as time of getting up, meal times etc. is rigid, with fixed 2-hour slots. The increment chosen - 5% - was arbitrary and further studies may be needed to discover whether there is any better increment. The increment may need to vary over the course of recovery. In the early days and weeks quite large increases will occur naturally, but over time the natural rate of change drops and a stable increment might be more applicable after the first 3 months. The visual feedback display seems appropriate, but again there may be better designs; there is always a compromise between detail and simplicity. Recent research suggests that feedback coupled with goal setting can be effective [11], and so an improvement in technology coupled with increasing knowledge may make the goal setting and feedback system more effective.

A third limiting factor arises from the funding and timing of inpatient rehabilitation in Hefei, which starts quite late after stroke and is limited to 2 or 3 weeks of inpatient rehabilitation, limiting the time the intervention can be applied. By the time a person is admitted, they have already established a pattern of behaviour. Also, it may take at least 1 week to become familiar with the device and its purpose and, because changing behaviour takes time, the intervention may be too short to lead to any detectable difference between the groups. It was not possible to provide the watch for use at home, mainly for practical reasons (daily data downloads and recharging). Ideally the intervention should be continued over many weeks.

The research funding was limited. The research data were collected by the ward doctors, who were specifically trained and collected the clinical data as part of their normal work. However, this limited the options of using more fixed procedures, for example when checking cognitive ability. This will not cause any bias, but may slightly limit generalizability.

Last, it has been assumed that increasing general, non-specific activity levels will lead to specific changes in mobility and independence is activities. This assumption is reasonable, but the strength of the relationship is unknown and a much larger study may be needed to show any actual benefit.

One strength is that, according to our calculations, the study is adequately powered; we will recruit about 200 patients. Second, the study is embedded with daily clinical routines in a busy hospital, such that if the intervention is effective, it should be easy to continue the intervention.

If this study does not show an effect, there will still be worthwhile knowledge generated. The study will give an estimate of variance in the measures used, which will help in future power calculations. It will discover whether a short episode of feedback on activity set against goals might have an effect. Failure to find an effect should not be taken as proving the intervention is ineffective, given the limitations identified. The study will give information about the feasibility of collecting data in a trial set within a standard rehabilitation programme in China (Additional file 1).

